**NB! Do not use ultrasonic nebulizers for the administration of the combination medication**

## **4. CLINICAL AND LABORATORY ASSESSMENT**

Clinical and laboratory examination of volunteers within 48 hours before the beginning of combination medication usage.

### **4.1. Complaints Assessment.**

### **4.2. Clinical Examination:**

Physical examination (assessment of the visible mucous membranes of the upper respiratory tract, auscultation and percussion of the lungs, palpation of the lymph nodes, abdominal examination and determination of the size of the spleen and liver, thermometry, BP, HR, RR).

### **4.3. Laboratory Tests:**

Detection of SARS-CoV-2 coronavirus RNA by RT-PCR in accordance with the "Interim Guidelines of the Ministry of Health of the Russian Federation on the Prevention, Diagnosis, and Treatment of the Novel Coronavirus Infection COVID-19, Version 5 (08.04.2020)".

## 5. **BENEFIT-RISK ASSESSMENT**

### 5.1. **Efficiency:**

The efficacy of the therapy will be assessed based on the analysis of the primary outcome - a development rate among healthy volunteers of the infectious process caused by the SARS-CoV-2 virus during the study, as confirmed by the detection of viral RNA in biological material using PCR according to the Temporary Guidelines of the Ministry of Health of the Russian Federation on the prevention, diagnosis, and treatment of the novel coronavirus infection COVID-19.

### 5.2. **Safety:**

The rate and intensity of the clinical manifestations of adverse events (AE).

The rate and intensity of deviations from the reference values of laboratory parameters and instrumental data

#### 5.2.1. Methods and time schedule for assessment, registration, and analysis of safety parameters

The development rate and intensity of AE will be assessed in the physical examination at each visit, as well as during and after each administration of the medicinal product.

The conclusion about the safety of the administered medication will be made after a statistical evaluation of all AEs, including serious AEs, which have revealed at least a possible relation with the administration of the pharmaceuticals used.

#### 5.2.2. Adverse events registration and reporting

##### Adverse events (AE)

The protocol requires the registration of all AEs that occur in the patient during and after administration of the medicinal product and until the end of the patient's participation in the trial.

An adverse event is defined as “any untoward medical occurrence in a patient in a clinical investigation who received a medicinal product; the event does not necessarily have to have a causal relationship with this treatment” (National Standard of the Russian Federation GOST R52379-2005 “Good Clinical Practice”).

An AE can be any symptom (including a clinically significant deviation of the laboratory measurement from the reference values), complaint, or disease, the time of occurrence of which does not exclude a causal relationship with the use of the investigational medicinal product, regardless of the existence of such a relationship.

AEs are classified by severity (nonserious or serious AEs), causal relationship with the investigational medicinal product (no/yes; if yes: probable, possible, unlikely, conditional, unclassifiable), and intensity (mild, moderate, severe).

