### Causal relationship between AEs and the investigational medicinal product:

The investigator will evaluate the relationship between the development of an adverse event and the investigational medicinal product as follows:

No - it is clearly and unconditionally related only with extraneous reasons and does not meet the criteria for an unlikely, possible, or probable relationship.

Yes - there is a reasonable causal relationship with the administered investigational product

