### Criteria:

- could have been caused by a clinical state or external factors or other prescribed treatments;
- a clear temporal relationship between discontinuation of the investigational medicinal product or dose reduction and improvement;
- recurrent upon repeated administration;
- corresponds to the known response to the investigational medicinal product.

The relationship between AEs and the investigational medicinal product will be assessed by a WHO scale, considering the design of the study.

Certain. Clinical manifestations of AEs and laboratory test abnormalities appear during the medicinal product intake and cannot be explained by diseases or other factors.

Probable. Clinical manifestations of AEs and laboratory test abnormalities have a reasonable time relationship to the medicinal product intake and are unlikely to be attributed to concomitant diseases or other factors.

Possible. Clinical manifestations of AEs and laboratory test abnormalities have a reasonable time relationship to the medicinal product intake; however, they could also be explained by concomitant diseases or the use of other pharmaceuticals and the influence of chemical compounds.

Unlikely. Clinical manifestations of AEs and laboratory test abnormalities have an improbable (but not impossible) time relationship to medicinal product intake; other factors (pharmaceuticals, diseases, chemical compounds) provide plausible explanations for the events.

Conditional. Clinical manifestations of AEs and laboratory test abnormalities related to the AEs are difficult to evaluate. More data for proper assessment are needed, or these additional data are under examination.

Unclassifiable. Reports suggesting an AE cannot be judged because the information is insufficient or contradictory.

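### The causality rules in Protocol section 5.2.2 do not agree: improbable and unassessable events are filed under a causal yes, and the certain category has no code

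*Protocol*

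**What the plan says.** The relevant statements are in sections 5.2.1, 5.2.2 and 6 of the Protocol.

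- **Code list (5.2.2, Adverse events).** Causality is recorded as no or yes, and the yes is subdivided: "if yes: probable, possible, unlikely, conditional, unclassifiable". That is five codes, without certain.
- **Definitions of no and yes (5.2.2, Causal relationship).** A no is reserved for an event that "does not meet the criteria for an unlikely, possible, or probable relationship". A yes means that "there is a reasonable causal relationship with the administered investigational product".
- **Criteria list (5.2.2, Criteria).** Four items follow the yes definition. The first is that the event "could have been caused by a clinical state or external factors or other prescribed treatments". The other three are improvement after withdrawal or dose reduction, recurrence on repeated administration, and agreement with the product's known response.
- **Scale (5.2.2, Criteria).** "The relationship between AEs and the investigational medicinal product will be assessed by a WHO scale", followed by six defined categories: certain, probable, possible, unlikely, conditional and unclassifiable. The first entry begins "Certain. Clinical manifestations of AEs and laboratory test abnormalities appear during the medicinal product intake".
- **Use of the classification.** Section 5.2.1 bases the safety conclusion on events showing "at least a possible relation" to the product. Section 6 presents adverse events by relationship, alongside overall counts of patients with events and of events.

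**The concern.** An investigator has to turn each event into a causality code, and the Protocol gives a code list, a yes/no definition and a scale that cannot all be followed at once. An event judged unlikely is a yes by the code list, does not meet the definition of yes, and is barred from no. An event judged certain has a definition but no entry in the code list. Conditional and unclassifiable events cannot yet be judged, or cannot be judged at all, yet they are filed under yes.

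This matters because safety is one of the two endpoints in section 2.2. The design in section 2.3 is an open-label cohort with no control group described, so no comparator rate is available to check attribution. The by-relationship results rest on the investigator's code. The fault also sits partly at data collection: a later analysis rule can choose which codes to pool, but it cannot recover certain events that were entered under another code.

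**Working it through.** No figure in the plan is at stake, so the check is a comparison of the rules.

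**Step 1. Place each of the six scale categories under each rule.**

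| Category (scale in 5.2.2) | Code list in 5.2.2 | Yes as defined in 5.2.2 | Threshold in 5.2.1, on the graded scale |
|---|---|---|---|
| Certain | no code | fits | counted |
| Probable | yes | fits | counted |
| Possible | yes | arguably fits | counted |
| Unlikely | yes | does not fit | not counted |
| Conditional | yes | not judged yet | not stated |
| Unclassifiable | yes | cannot be judged | not stated |

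**Step 2. Compare the sets.** The code list's yes holds 5 codes. The 5.2.1 threshold on the six-category scale holds 3 (certain, probable, possible). The two sets share 2 (probable, possible). So 5 − 2 = 3 codes are a yes without clearly reaching the threshold, and 3 − 2 = 1 category reaches the threshold without having a code in the list.

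**Step 3. Is the placing of unlikely an isolated slip?** No. The definition of no also shuts out unlikely events, so the code list and that definition agree on a narrow no. The clash is with the wording of yes and with the scale's own description of unlikely, which combines improbable timing with plausible other explanations.

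**Step 4. Read the first criterion.** That something else could have caused the event is a point against a drug cause; the other three items are points for one. It runs opposite to the certain and probable definitions, which require that other causes do not or are unlikely to explain the event. It is compatible with possible, whose definition allows another explanation.

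**Step 5. Trace the effect on the outputs.**

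- Section 6, by relationship: at the yes/no level, unlikely, conditional and unclassifiable events appear as related. At the level of individual codes they stay visible, but certain has no row if the five-code list is used.
- Section 5.2.1, safety conclusion: applied to the graded codes, the threshold drops unlikely under either list. A certain event entered as probable for want of a code would still count. Conditional and unclassifiable events are left undecided.
- Section 6, overall adverse event and serious adverse event frequency: does not use causality, so no effect.

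**The case against.** The strongest reply is that this is a drafting mismatch with little consequence. The Protocol directs that a WHO scale be used and defines it in full, so the earlier list may be only a summary in brackets. The adverse event registration form is not shown, so it is not known that its codes omit certain. The main safety measures, rate and intensity, do not depend on causality. Choosing which codes to pool is commonly left to the SAP, which is not at hand.

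Much of this stands, and it limits the point. Four stronger readings are tempting and are not supported:

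- *That the safety conclusion would be inflated by unlikely events.* Nothing in the Protocol bases that conclusion on the yes/no field. The stated threshold is "at least a possible relation", and unlikely events fall below it under either list.
- *That certain events could not be recorded at all.* The scale defines the category, and the form may carry it. What is shown is only that the code list in the text leaves it out.
- *That the first criterion is inverted through a lost negation.* This is plausible but unproven. The criteria have their own heading, no sentence says each must hold for a yes, and the item fits possible as written.
- *That different sites would code differently.* The Protocol does not describe several sites.

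The reply does not remove the contradiction. No sentence says that the scale replaces the code list, and the definition of no repeats the placing of unlikely. An SAP can decide how to pool codes, but it cannot make the Protocol's own definitions agree at the point where events are coded.

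**Conclusion.** The point holds as an internal inconsistency of minor severity. On the Protocol's own definitions, three of the five codes under yes do not belong there, one of the six defined categories has no code in the list, and one of the four criteria points the opposite way to the rest. The related-event count is therefore not uniquely defined.

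The exposure is mainly in the section 6 tabulation by relationship, on the assumption that it uses the yes/no level; section 6 does not say which level applies. For the section 5.2.1 conclusion, the open question is confined to conditional and unclassifiable events, provided the threshold is applied to the graded codes. Overall adverse event and serious adverse event incidence stands. The number of events affected cannot be given, because the Protocol contains no expected distribution of causality codes.

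**What to change.** Make four wording changes in section 5.2.2, with a cross-reference from sections 5.2.1 and 6.

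1. Use the six scale categories as the only causality code list, replacing the five codes now under yes.
2. Revise the definitions of no and yes to match. In particular, the definition of no must stop excluding unlikely events; otherwise it would conflict with the next item.
3. State that, for sections 5.2.1 and 6, related means certain, probable or possible; unlikely is not related; conditional and unclassifiable are reported separately as not assessable.
4. Mark the first criterion as a consideration against relatedness, compatible with possible at most, rather than as support for a yes. It should not be turned into a requirement that no other cause can explain the event, because that would exclude the possible category, which item 3 counts as related.

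The cost is wording only, plus the code list on the adverse event form if that form follows the five-code version. No new data are needed.

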##### Serious adverse events (SAEs)

In the framework of this protocol and in accordance with legal requirements (National Standard of the Russian Federation GOST R52379-2005 “Good Clinical Practice” dated September 25, 2005), a SAE is defined as any adverse medical event that, regardless of the dose of the medicinal product, results in death, is immediately life-threatening, requires or prolongs patient hospitalization, results in a persistent or significant disability or incapacity, or is a congenital anomaly or birth defect.

### Intensity of AE

The intensity of the AE should be judged based on the following classification:

- Level 1 - Mild: an adverse event that is easily tolerated by the patient, causing minimal inconvenience and not interfering with the patient's daily activities.
- Level 2 - Moderate: an adverse event that causes discomfort and interferes but does not impede the patient's daily activities.
- Level 3 - Severe: an adverse event that impedes normal daily activities.

### Causal relationship between AEs and the investigational medicinal product:

The investigator will evaluate the relationship between the development of an adverse event and the investigational medicinal product as follows:

No - it is clearly and unconditionally related only with extraneous reasons and does not meet the criteria for an unlikely, possible, or probable relationship.

Yes - there is a reasonable causal relationship with the administered investigational product

### Criteria:

- could have been caused by a clinical state or external factors or other prescribed treatments;
- a clear temporal relationship between discontinuation of the investigational medicinal product or dose reduction and improvement;
- recurrent upon repeated administration;
- corresponds to the known response to the investigational medicinal product.

The relationship between AEs and the investigational medicinal product will be assessed by a WHO scale, considering the design of the study.

Certain. Clinical manifestations of AEs and laboratory test abnormalities appear during the medicinal product intake and cannot be explained by diseases or other factors.

Probable. Clinical manifestations of AEs and laboratory test abnormalities have a reasonable time relationship to the medicinal product intake and are unlikely to be attributed to concomitant diseases or other factors.

Possible. Clinical manifestations of AEs and laboratory test abnormalities have a reasonable time relationship to the medicinal product intake; however, they could also be explained by concomitant diseases or the use of other pharmaceuticals and the influence of chemical compounds.

Unlikely. Clinical manifestations of AEs and laboratory test abnormalities have an improbable (but not impossible) time relationship to medicinal product intake; other factors (pharmaceuticals, diseases, chemical compounds) provide plausible explanations for the events.

Conditional. Clinical manifestations of AEs and laboratory test abnormalities related to the AEs are difficult to evaluate. More data for proper assessment are needed, or these additional data are under examination.

Unclassifiable. Reports suggesting an AE cannot be judged because the information is insufficient or contradictory.

### Terms used with respect to the investigational medicinal product:

An adverse event (“side effect”) means any untoward medical occurrence in the subject of the study that is associated with the use of the registered medicinal product in the doses recommended in the instructions for medical use of the product.

Unanticipated adverse event - an adverse event, the nature or severity of which is not consistent with known product information, for example, with instructions for medical use in the case of a registered medicinal product.

Severe unanticipated adverse event (SUAE) - an unanticipated adverse event that is characterized by features of SAE.

#### Registering adverse events

Responsibility for registering AEs in a clinical trial lies with the research doctor. At each visit, the researcher registers all objectively observed or subjectively described AEs in primary documents and individual patient records, filling out the relevant pages of individual patient records and informing the classification of AEs (severity, intensity, relationship with the administration of the medicinal product).

Any available information related to the registered AE, for example, the results of diagnostic tests (laboratory tests, ECG, etc.) should also be attached to the individual patient's record.

#### Reporting adverse events/serious adverse events

In the case of an AE, the investigator should describe it in as much detail as possible in the primary documentation of the patient, register the AE in the individual patient's record, and fill in the AE Registration Form (Appendix to the individual patient's record).

The following shall be registered in the documents: the clinical manifestation of the AE, the time of occurrence and resolution of the AE, the severity/intensity of the AE, an unanticipated or previously described/known AE, possible relationship with the investigational medicinal product/benchmarking medicinal product administration, relationship with the administration method of the medicinal product, measures taken in relation to the patient and use of the pharmaceutical, drug therapy for the AE, and outcome/resolution of the AE.

Upon receipt of additional information on the development/resolution of the AE, the investigator should register it in the primary documentation and in the previously launched AE Registration Form.

In the case of emerging new symptoms that are not associated with a previously emerged AE, the investigator should launch a new AE form.

In case of the development of an SAE, it should also be registered in the primary documentation and the patient's individual record; the SAE Registration Form shall be filled out (Appendix to the Individual patient's record).

All AE/SAE Registration Form fields should be filled in. In the absence of information, the N/D field is checked (no data, that is, unknown); alternatively, a dash is drawn in the field (for example, in the "date" field), or a record is made that a given procedure was not performed.

## 6. STATISTICAL ANALYSIS

The methods for statistical analysis of the obtained data are determined by the nature, type, and distribution of the data. The applicability of a number of statistical methods will be evaluated upon the completion of the data collection due to the unknown distribution, sample uniformity, etc. In the course of the analysis, the list of methods used can be expanded if necessary for high-quality data processing.

Statistical processing of data obtained in the study will be carried out using statistical programs or other special software that would ensure high quality of the results. Interval (quantitative) data will be described using the arithmetic mean, standard deviation, median, lower (25%) and upper (75%) quartiles, minimum and maximum values. Categorical (qualitative) data will be described using absolute and relative frequencies. To compare normally distributed quantitative data, standard parametric criteria shall be employed: Student's t-test for dependent/independent samples and analysis of variance (ANOVA) for repeated measurements. For the comparison of quantitative data that are not normally distributed, standard nonparametric tests shall be employed. The frequencies of the variables will be compared between the groups using Pearson's  $\chi^2$  test or Fisher's exact test.

AEs will be analyzed based on the frequency of adverse events/serious adverse events. Adverse events registered within the study will be presented by incidence rate (the number of patients with AEs and the number of such AEs in the group). AEs will also be presented by their intensity and relationship with the administration of the combined medicinal product.

Regardless of the reason for the termination of the study, the data of all enrolled healthy volunteers will be taken into account when analyzing the efficiency and safety of the investigational therapy.

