### **2.2. Endpoints**

- 3.2.1 Determine the frequency of laboratory confirmed SARS-CoV-2 cases, defined by RT-PCR positivity within 28 days observational period, in high risk population with routine COVID-19 positive contacts.
- 3.2.2 Evaluation of the safety of aerosol combination therapy as the pre-exposure prophylaxis for COVID-19.

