### **2.3. Design**

The study is intended as a low-interventional prospective open-label clinical study of aerosol combination therapy in a cohort of healthy adult volunteers regularly exposed to COVID-19 positive contacts.

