### **2.6. Exclusion Criteria**

Healthy volunteers cannot be included in the trial if they meet at least one of the following criteria.

2.6.1. Criteria related to the disease:

Detection of SARS-CoV-2 virus RNA by polymerase chain reaction (PCR) in biomaterial samples and/or positive enzyme-linked immunosorbent assay ELISA IgM and ELISA IgG to the virus in a healthy volunteer;

2.6.2. Criteria related to the combination medication, previous therapy and concomitant therapy:

Hypersensitivity or individual intolerance to the components of the combination therapy according to the medical history.

2.6.3. Criteria related to the concomitant pathology:

According to the medical history and physical examination:

- any diseases or conditions that, in opinion of the investigator, would make it difficult to interpret the results of treatment or may limit the participation of a healthy volunteer in the study.

According to screening laboratory tests:

- related to the compliance of healthy volunteers in the study;
- any diseases or conditions that, in opinion of the investigator, would make it difficult to interpret the results of treatment or may limit the participation of healthy volunteers in the study;

Healthy volunteers who, in the opinion of the investigator, are obviously or likely unable to understand and evaluate the information regarding this study within the process of signing the informed consent form, in particular regarding the expected risks and possible discomfort.

The inability or unwillingness of a healthy volunteer to follow the rules for carrying out the study and participating in a clinical trial.

2.7. **Early Discontinuation Criteria**

2.7.1. A healthy volunteer will be excluded from the study if SARS-CoV-2 virus RNA is detected in biomaterial samples by a polymerase chain reaction (PCR) for COVID-19 or if enzyme-linked immunosorbent assay (ELISA) IgM and ELISA IgG results are positive.

2.7.2. A healthy volunteer may withdraw their consent to participate in the study at any time and without giving reasons. The investigator may also decide on early discontinuation of the participation of a healthy volunteer in the study at any time if the patient's condition requires it.

2.7.3. Main reasons for early discontinuation of participation of a healthy volunteer in the study:

Individual intolerance to the combination medication or any of its components;

Failure to meet the inclusion and exclusion criteria;

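### Simple frequencies over all enrolled volunteers would be diluted by those who leave without a positive PCR (infection) and by those never dosed (adverse events); the effect is small unless such volunteers are numerous

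*Protocol*

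**What the plan says.** Section 6 of the protocol (Statistical Analysis) names one population for both purposes: "the data of all enrolled healthy volunteers will be taken into account when analyzing the efficiency and safety of the investigational therapy". For binary outcomes it gives one summary: "Categorical (qualitative) data will be described using absolute and relative frequencies". Adverse events are to be shown as "the number of patients with AEs and the number of such AEs in the group". The section leaves room for more methods, since "the list of methods used can be expanded if necessary for high-quality data processing". It does not define enrolled, state a denominator, or say how a volunteer with missing swabs or no dose is counted.

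The primary endpoint (section 2.2) is a frequency over a fixed horizon, "defined by RT-PCR positivity within 28 days observational period". The Study Plan in Appendix 1 schedules PCR at screening, on Days 1, 7 and 14, and in follow-up (Days 21 and 28). The design (section 2.3) is a "low-interventional prospective open-label clinical study of aerosol combination therapy in a cohort of healthy adult volunteers", so there is no control arm. Section 2.4 takes 11.1% as the outside reference rate.

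Early exit is foreseen. Under 2.7.2, "A healthy volunteer may withdraw their consent to participate in the study at any time and without giving reasons". Section 2.7.3 adds intolerance, adverse events and investigator judgement, and no PCR after exit is described. Section 5.2.2 defines an adverse event as "any untoward medical occurrence in a patient in a clinical investigation who received a medicinal product".

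**The concern.** The outcome has a 28-day horizon, but some volunteers may be observed for less. Suppose a volunteer withdraws after the Day 1 swab and the reported frequency is positives over all enrolled. That volunteer then adds one to the denominator for the whole period and can no longer add to the numerator. The estimate falls although nothing was learned about that person's risk.

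In a randomised comparison both arms would lose cases this way. Here the single cohort is set against an outside rate, so lost follow-up moves the result towards apparent efficacy.

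The safety side is parallel. Consent is taken at screening and eligibility is rechecked at Visit 1, so a volunteer can be enrolled and never inhale the product. Such a person can hardly have an adverse event as section 5.2.2 defines it, yet would enlarge the denominator of every adverse-event percentage.

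**Working it through.** **Inputs from the protocol.** Reference rate 11.1%, target 3%, alpha 0.05, N = 96 (section 2.4); horizon 28 days (2.2); swab days 1, 7, 14, 21, 28 (Appendix 1).

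**Assumptions, not in the protocol.** Share *d* of volunteers leaving without a positive PCR: 10% or 20%. Constant hazard of infection. Leaving unrelated to infection. Success rule of 4 or fewer cases in 96, the largest count whose exact lower-tail probability under 11.1% does not exceed 0.025.

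**Step 1: the plan's own figure.** The stated beta error of 0.85 works only if read as power. With a two-sided one-sample test of a proportion:

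n = [(1.960·√(0.111·0.889) + 1.036·√(0.03·0.97)) / (0.111 − 0.03)]² = 95.7, rounded up to 96.

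The stated size is reproduced with no allowance for dropout.

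**Step 2: complete follow-up.** P(X ≤ 4 | 96, 0.111) = 1.45%. This is the false-efficacy chance for an inert product.

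**Step 3: leaving evenly over 28 days, counted over all enrolled.** Hazard h = −ln(0.889)/28 = 0.00420 per day. A leaver can be found positive only up to the last swab attended:

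| Leaving time (days) | Last swab | Chance of a detected case, 1 − exp(−h·day) |
|---|---|---|
| 0–1 | none | 0 |
| 1–7 | Day 1 | 0.0042 |
| 7–14 | Day 7 | 0.0290 |
| 14–21 | Day 14 | 0.0571 |
| 21–28 | Day 21 | 0.0845 |

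The mean, weighted by interval length (1, 6, 7, 7, 7 of 28), is 0.0435. The expected rate is (1 − d)·0.111 + d·0.0435.

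**Step 4: all leavers go before the Day 7 swab.** Neglecting the small Day 1 yield, the expected rate is (1 − d)·0.111.

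| Scenario | Expected rate | P(X ≤ 4 of 96) |
|---|---|---|
| Complete follow-up | 11.1% | 1.45% |
| 10% leave evenly | 10.4% | 2.3% |
| 20% leave evenly | 9.8% | 3.7% |
| 10% leave before Day 7 | 10.0% | 3.1% |
| 20% leave before Day 7 | 8.9% | 6.4% |

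**Step 5: what censoring restores.** Say 10 of 96 leave just after a negative Day 1 swab. The expected number of cases among the other 86 is 86 × 0.111 = 9.5. Over all enrolled this is 9.5/96 = 9.9%. With the 10 censored at Day 1 it is 9.5/86 = 11.1%.

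**Step 6: the opposite direction.** One volunteer positive on the Day 1 swab and counted over all enrolled adds 1/96 = 1.04 percentage points. At a true 3%, losing 10% with no follow-up removes only 3.0 − 2.7 = 0.3 points.

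**Step 7: safety.** A true adverse-event rate of 5% shows as 0.05 × 0.90 = 4.5% if 10% of the denominator was never dosed. With no events of a given type, the one-sided 95% upper limit is 1 − 0.05^(1/n): 3.1% for n = 96 and 3.4% for n = 86. Ten undosed volunteers therefore make the stated limit 0.3 points too low.

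**The case against.** A reader might infer that the protocol counts every early leaver as uninfected and every undosed volunteer as event-free, so that both rates are certain to be too low. The text does not support this, for three reasons.

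- Section 6 states no denominator and no rule for a missing PCR. Taking everyone's data into account is compatible with a censored estimate, and the list of methods may be extended.
- Some leavers are events. A positive PCR is itself a reason for removal (2.7.1), and intolerance and adverse events are reasons to leave (2.7.3). Keeping all enrolled is what retains those cases, and it guards against reporting completers only.
- The direction is not certain. As Step 6 shows, a single Day 1 positive can outweigh the dilution.

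The size can be contested too. The dropout shares and the 4-of-96 rule are assumptions. Section 2.4 expects nearly all volunteers to complete, and 10% leaving evenly still gives 2.3%, inside the 2.5% tail. On safety, screening lasts at most two days, so undosed volunteers should be few, and section 2.4 bases its safety precision on the treatment group.

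Analysis sets and missing-data rules are often left to a statistical analysis plan, so their absence alone would be no finding. What stands is narrower. The protocol does write one all-enrolled population for both efficacy and safety, and a simple frequency is the only summary it names for a 28-day outcome from which volunteers may exit at any time. Followed literally, that combination dilutes.

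**Conclusion.** The point holds conditionally. If the infection frequency is positives over all enrolled, volunteers who leave without a positive PCR dilute it; if adverse-event percentages use the same denominator, never-dosed volunteers dilute them. With near-complete follow-up, as the protocol expects, the effect is close to nil. With material dropout it matters: in the assumed setting the false-efficacy chance goes from 1.45% to between 2.3% and 6.4%, the upper end requiring 20% to leave before Day 7. The safety effect is modest, 3.4% against 3.1% for a zero-event limit with ten undosed volunteers. These figures rest on an inert product at 11.1%, a constant hazard, leaving unrelated to infection, and a success rule the protocol does not state. The correction is still worth making, because it is cheap and leaves the estimate unchanged when nobody leaves and everyone is dosed.

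**What to change.** 1. **Primary estimate.** Keep all dosed volunteers in the analysis. Estimate the frequency as the Kaplan-Meier cumulative incidence at Day 28, calculated by swab day, with a 95% interval. Volunteers removed for a positive PCR count as cases; leavers without one are censored at their last valid swab. With complete follow-up this equals the simple proportion, and an exact interval then applies.
2. **Sensitivity analysis.** Repeat with leavers who had no positive PCR counted as infected. Censoring assumes that leaving is unrelated to infection; if volunteers leave because they fall ill, the censored estimate is too low as well.
3. **Safety.** Report adverse-event percentages over volunteers who inhaled at least one dose, in line with the definition in section 5.2.2.
4. **Wording.** Define enrolled, and say how a positive Day 1 swab is counted.

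The cost is analysis wording only, since visit dates and PCR results are already recorded at each visit. The downside is a slightly higher and wider estimate when volunteers leave, and reliance on uninformative censoring, which the sensitivity analysis is there to test.
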